### Interventions

#### Blood glucose control

The subjects in the “Adjust Zang-fu and Arouse Spirit” electroacupuncture group and the sham acupuncture group will receive routine hypoglycemic therapy of Western medicine, and their blood glucose will be strictly monitored to keep their blood glucose stable.

#### Electroacupuncture intervention

In this trial, treatment strategies were developed by consensus with experienced acupuncture practitioners and radiologists. There are two groups: “Adjust Zang-fu and Arouse Spirit” electroacupuncture group or sham electroacupuncture group. The location and manipulation of fixed acupoints and nonacupoints are shown in Table 2. All electroacupuncture treatment sessions will be performed by four Chinese Medicine Practitioners acupuncturists registered in China with at least 3 years of clinical experience in acupuncture practice. Acupuncturists will also receive training prior to this trial. The training course will include the location of acupoints, needle manipulation skills, and communication skills. When the acupuncturists are able to pass the trial training examination, they will be admitted to participate in the trial.

**Table 2 Tab2:** Locations and manipulations of the acupuncture points selected in this study

Group	Acupoints	Location	Manipulation
“Adjust Zang-fu and Arouse Spirit” electroacupuncture group	Baihui (GV20)	In the head, the front of the forehead is straight up to 5 cun	Subcutaneous insertion to a depth of 0.5-0.8 cun (12.5–20 mm) with manipulation for the de-qi
	Shenting (GV24)	In the head, the front of the forehead is straight up to 0.5 cun	Subcutaneous insertion to a depth of 0.5–0.8 cun (12.5–20 mm) with manipulation for the de-qi
	Feishu (BL13)	In the spinal region, under the spinous process of the third thoracic vertebrae, 1.5 cun beside the posterior midline	Oblique insertion to a depth of 0.5–0.8 cun (12.5–20 mm) with manipulation for the de-qi
	Pishu (BL20)	In the spinal region, under the spinous process of the 11th thoracic vertebrae, 1.5 cun beside the posterior midline	Oblique insertion to a depth of 0.5–0.8 cun (12.5–20 mm) with manipulation for the de-qi
	Shenshu (BL23)	In the spinal region, under the spinous process of the second lumbar spine, 1.5 cun beside the posterior midline	Puncture perpendicularly to a depth of 0.5–1.0 cun with manipulation for the de-qi.
	Zusanli (ST36)	Three inches below the patella between the anterior tibia and the extensor digit rum longus muscle	Puncture perpendicularly to a depth of 1–1.5 cun with manipulation for the de-qi
	Sanyinjiao (SP6)	On the medial side of the leg, 3 cun above the tip of the medial malleolus, posterior to the medial border of the tibia	Puncture perpendicularly to a depth of 1.0 cun with manipulation for the de-qi
	Hegu (LI4)	On the back of the hand, at the midpoint of the radial side of the second metacarpal bone	Puncture perpendicularly to a depth of 0.5–1.0 cun with manipulation for the de-qi
	Taichong (LR3)	In the posterior recess of the 1st metatarsal space	Puncture perpendicularly to a depth of 0.5–0.8 cun (12.5–20 mm) cun with manipulation for the de-qi
Sham-electroacupuncture group	Beside GV20	It is 0.5 cun (12.5 mm) to the right of GV20	Needled through adhesive pads to the skin (for the fixation of needles) without penetrating the skin and manipulation for the de-qi
	Beside GV24	It is 0.5 cun (12.5 mm) to the right of GV24	Needled through adhesive pads to the skin (for the fixation of needles) without penetrating the skin and manipulation for the de-qi
	Beside BL13	It is located 1 cun outside BL13	Needled through adhesive pads to the skin (for the fixation of needles) without penetrating the skin and manipulation for the de-qi
	Beside BL20	It is located 1 cun outside BL20	Needled through adhesive pads to the skin (for the fixation of needles) without penetrating the skin and manipulation for the de-qi
	Beside BL23	It is located 1 cun outside BL23	Needled through adhesive pads to the skin (for the fixation of needles) without penetrating the skin and manipulation for the de-qi
	Beside ST36	It is located 1 cun backward of ST36	Needled through adhesive pads to the skin (for the fixation of needles) without penetrating the skin and manipulation for the de-qi
	Beside SP6	It is located 1 cun backward of P6	Needled through adhesive pads to the skin (for the fixation of needles) without penetrating the skin and manipulation for the de-qi
	Beside LI4	It is located 1 cun in front of LI4	Needled through adhesive pads to the skin (for the fixation of needles) without penetrating the skin and manipulation for the de-qi
	Beside LR3	It is located 1 cun backward of LR3	Needled through adhesive pads to the skin (for the fixation of needles) without penetrating the skin and manipulation for the de-qi

#### “Adjust Zang-fu and Arouse Spirit” electroacupuncture treatment group

When the patients are in a comfortable sitting position, all acupoints will be punctured by filiform needles (0.3 mm × 25 mm/0.3 mm × 40 mm, Hwato Brand, Suzhou Medical Appliance Factory, China). Then, lifting, thrusting, twisting, and rotating manipulations will be applied on the needles until the *de-qi* sensation is achieved. After achieving the *de-qi* sensation, electric stimulators (SDZ-V electroacupuncture apparatus, Suzhou Medical Appliance Factory, China) will be attached to needles at the GV20-GV24, unilateral BL13-BL23 and SP6-LR3 points, and a continuous wave of 2 Hz/100 Hz frequency and an intensity of 0.1–1.0 mA will be applied.

#### Sham-electroacupuncture treatment group

Nonacupoints will be needled through adhesive pads to the skin (for the fixation of needles) without penetrating the skin using 1 cun blunt needles. The sham electrode lines look identical to the real lines but with the inner metal wire cut off. The electric stimulators will connect the beside GV20-beside GV24, unilateral beside BL13-beside BL23, and beside SP6-beside LR3. The needle parameters were the same as those for the electroacupuncture group. When turned on the electroacupuncture instrument, the electric acupuncture apparatus looks normal but has no current output.

For both groups, the needles will be retained for 30 min for each treatment session. The participants will be treated with electroacupuncture 5 times a week, followed by a 2-day rest interval for 8 successive weeks, with 40 sessions for each patient in total.

### MRI scanning procedure

The Siemens 3.0 T Magnetom Verio MRI system (Siemens Medical, Erlangen, Germany) with a 32-channel head coil will be used to obtain MRI data at the Affiliated Hospital of Changchun University of Chinese Medicine (Changchun, China). To avoid head movement, foam pads will be used to fix the participants’ heads. The fMRI data will be acquired with a single-shot gradient recalled echo planar imaging sequence with the following parameters: repetition time (TR)/echo time (TE) =3000 ms/30 ms, flip angle = 85, field of view (FOV) = 220 mm × 220 mm and slice thickness = 3 mm. Magnetic resonance spectroscopy (MRS) data will be acquired with 3D multivoxel proton magnetic resonance spectroscopy with the following parameters: repetition time (TR)/echo time (TE) =1750 ms/144 ms, slice thickness = 5 mm and repeat time = 128.

### Outcome measures

The time schedule of enrollment, interventions, and assessments of participants are shown in Fig. 2. The following outcomes will be assessed by independent assessors.

**Fig. 2 Fig2:**
[figure not shown]
Timetable of treatment and outcome collection

#### Primary outcomes

The primary outcomes include whole-brain structure and function evaluated using fMRI, metabolites in the basal ganglia evaluated using MRS, and cognitive function assessed using the MoCA and CDR.

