**Methods:**

This clinical research will be a randomized, sham-controlled pilot trial. Eligible participants will be randomly assigned to the intervention group (*n* = 60) and the control group (*n* = 30). The intervention group will be divided into the “Adjust Zang-fu and Arouse Spirit” electroacupuncture group (*n* = 30) and sham electroacupuncture group (*n* = 30). All participants will continue to receive routine hypoglycemic therapy. The treatment period is the same in both groups. The primary outcomes include functional magnetic resonance imaging (fMRI), magnetic resonance spectroscopy (MRS), Montreal Cognitive Assessment Scale (MoCA), and Clinical Dementia Rating (CDR). The secondary outcomes include blood glucose and blood lipid tests, Instrumental Activities of Daily Living Scale (IADL), Hachinski Ischemic Scale (HIS), Self-Rating Anxiety Scale (SAS), and Self-Rating Depression Scale (SDS). Outcomes will be assessed at baseline and before and after treatment, and adverse events will be examined. Inter- and intragroup analyses will be performed.

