### Setting of the study

This clinical trial will be conducted at the third Affiliated Hospital of Changchun University of Chinese Medicine (Changchun, China). Eligible participants will be randomly assigned to the intervention group (*n* = 60) and the control group (*n* = 30). The intervention group will be divided into the “Adjust Zang-fu and Arouse Spirit” electroacupuncture group (*n* = 30) and sham electroacupuncture group (*n* = 30). The total observation period will include a − 3~0-day baseline selection period, an 8-week treatment period, and a 6-month follow-up period. They will receive 40 sessions of electroacupuncture or sham electroacupuncture treatment over 8 weeks (five sessions per week). Assessments will be conducted at baseline and at 4 and 8 weeks after randomization, as well as at 1, 2, 3, and 6 months after treatment. Figure 1 illustrates the study flowchart. This protocol will be reported according to the SPIRIT 2013 [17] statement of recommendations for intervention trials: Defining Standard Protocol Items for Clinical Trials. The trial process was designed according to the STRICTA 2015 [18] report (Table 1).

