### Sample size estimation

The sample size was calculated based on the MoCA scale score as the primary outcome. The sample size was calculated based on the noninferiority comparison of the two groups: *α* = 0.025, 1−*β* = 0.80, *Δ* = − 0.1, which was calculated by PASS software with *n* ≈ 24. Because there was partial shedding in the treatment process, the shedding rate was 20%, and thus, it was appropriate to increase the sample size and take *n* = 30 cases per group. Therefore, 30 cases per group were needed, totaling 90 patients in 3 groups.

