### Statistical analysis

#### Clinical data analysis

Statistical analysis of the clinical outcomes will be performed using SPSS 24.0 statistical software. All statistical tests will be bilateral, and *p* < 0.05 will be considered statistically significant. For clinical information, data will be presented as the mean ± standard deviation. Student’s *t* test and the chi-square test will be used to compare group differences at baseline. A paired *t* test will be used to compare the clinical outcomes within the groups. Analysis of variance and the Wilcoxon rank-sum (if normality is violated) will be used to compare the clinical feature changes between groups. The clinical data, including MoCA, CDR, HbA1c, TC, TGs, HDL-C, and LDL-C, will be converted to domain z scores for correlational analysis with imaging data. Missing data for the primary outcome will be imputed using the multiple imputation method.

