In addition, there are no exact and effective drugs or methods for the treatment of DCI in modern medicine, mostly starting from improving symptoms and delaying the disease. On the basis of controlling blood glucose and correcting the disorder of lipid metabolism, drugs to improve the function of brain cells are added for combined treatment, but long-term use easily produces side effects. Related studies have confirmed the important role of acupuncture in the prevention and treatment of diabetes and its complications [13, 27]. However, to date, there have been no properly designed randomized, sham-controlled pilot trials at home or abroad to provide clear evidence to prove the effectiveness of acupuncture in the treatment of DCI and to explain its related mechanism. The intervention method of this study was “Adjust Zang-fu and Arouse Spirit” electroacupuncture therapy, which is based on the previous research results of the research group and the TCM etiology and pathogenesis of DCI. It has the functions of harmonizing Zang-fu organs, freeing *qi* and blood, arousing the brain and regulating spirit. In the early stage, the research group applied this acupuncture method to the clinical treatment of DCI, showing a good clinical effect. At the same time, to eliminate the placebo effect of electroacupuncture, a sham electroacupuncture group was set up, but double-blinding could not be achieved because of the particularity of the electroacupuncture operation.

The main evaluation indicators of this study include brain imaging results and two cognitive assessment scales, and the secondary evaluation indicators include blood glucose and blood lipid detection and four related scales. The time point of evaluation included one evaluation before the treatment period, two evaluations in the treatment period and four evaluations in the follow-up period, for a total of seven evaluations. The brain imaging data of the patients were analyzed at the individual level, and the correlations between the brain imaging, scale results, and test results were analyzed. The purpose of this study was to analyze the changes in brain structure and function in patients with DCI and to explore the therapeutic effect of “Adjust Zang-fu and Arouse Spirit” electroacupuncture on DCI and its correlation with the changes in brain structure and function in patients with DCI.

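### Four unranked primary outcomes conflict with a sample size built on MoCA as the primary outcome, and no primary visit is named

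*Protocol article*

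**What the plan says.** The Primary outcomes section names two imaging outcomes first: "The primary outcomes include whole-brain structure and function evaluated using fMRI, metabolites in the basal ganglia evaluated using MRS". Two scales then complete the list, under the heading of cognition: "cognitive function assessed using the MoCA and CDR". No order or hierarchy is given. The abstract repeats the list of four, and the Discussion describes imaging plus two cognitive scales as the main indicators.

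The Sample size estimation section says otherwise: "The sample size was calculated based on the MoCA scale score as the primary outcome". The Clinical data analysis section also uses the singular when it describes imputation for the primary outcome, without saying which outcome that is.

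On timing, Setting of the study says: "Assessments will be conducted at baseline and at 4 and 8 weeks after randomization, as well as at 1, 2, 3, and 6 months after" the end of treatment. The Discussion counts one evaluation before treatment, then "two evaluations in the treatment period and four evaluations in the follow-up period, for a total of seven evaluations". The abstract gives a different picture: "Outcomes will be assessed at baseline and before and after treatment". None of these places says which visit decides the primary comparison. The timetable of outcomes by visit is in Fig. 2, which is not shown in the text available.

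On the decision rule, Clinical data analysis makes all tests two-sided and says that p below 0.05 "will be considered statistically significant". The Neuroimaging data analysis section lists tests but gives no threshold.

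**The concern.** The protocol gives two incompatible answers to the question of what is primary: four outcomes of equal rank, or MoCA. Two of the four are not single measures. Whole-brain structure and function covers many regions, and the metabolites are not named.

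Without a ranking and without a primary visit, both the outcome and the time point on which the trial is judged could be settled after the data are seen. A significant result on any one of several tests could then be presented as a positive primary result, and the 5% error rate would no longer apply to that claim. Nor does the sample size support four primary claims, because it was worked out for one.

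**Working it through.** **The plan's own figure.** The sample size section gives about 24 per group and 20% dropout, hence 24 / (1 − 0.20) = 30 per group and 3 × 30 = 90 in total. These steps reproduce. The 24 itself cannot be checked, because no standard deviation or expected difference is stated; that is a separate matter. What counts here is that the calculation uses one outcome and makes no allowance for several. The plan states no familywise error figure, so there is none to reproduce.

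**Inputs.** Four primary outcomes (Primary outcomes); six post-baseline evaluations, at weeks 4 and 8 and at 1, 2, 3 and 6 months after treatment (Setting of the study); 0.05 two-sided per test (Clinical data analysis, carried over to imaging as an assumption). I take one between-group test per outcome per visit, with all null hypotheses true.

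**Formula.** For k independent tests, the chance of at least one false positive is 1 − 0.95^k. Correlated cases come from simulating multivariate normal test statistics (100,000 draws). The assumed correlation is 0 to 0.5 between outcomes and, where there is more than one visit, 0.5 to 0.9 between visits.

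| Schedule assumed | Tests | Independent | Correlated |
|---|---|---|---|
| MoCA only, one visit | 1 | 5% | – |
| Four outcomes, one visit | 4 | 1 − 0.95^4 = 18.5% | 15.6% at outcome correlation 0.5 |
| MoCA only, six visits | 6 | 1 − 0.95^6 = 26.5% | 11–21% |
| Four outcomes, two visits | 8 | 1 − 0.95^8 = 33.7% | 21–32% |
| MoCA and CDR at six visits, fMRI and MRS once | 14 | 1 − 0.95^14 = 51.2% | 24–43% |
| Four outcomes, six visits | 24 | 1 − 0.95^24 = 70.8% | 31–60% |

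The third row shows that naming MoCA without naming a visit would not be enough if it is tested at every visit.

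**Direction.** These figures count false positives either way. Counting only those that favour treatment, where the nominal rate is 2.5%, four independent tests give 1 − 0.975^4 = 9.6% and 24 give 1 − 0.975^24 = 45.6%.

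**Keeping all four as primary.** Bonferroni needs 0.05 / 4 = 0.0125 per test. As an illustration, take a superiority design with 80% power at 24 per group and two-sided 0.05. The standardised effect is (1.960 + 0.842) × √(2/24) = 0.81. At 0.0125 its power falls to about 62%. Restoring 80% takes 35 per group, and 35 / 0.80 = 43.75, so 44 per group after dropout against the 30 planned.

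**The case against.** - **A pilot with mechanistic aims.** The trial is presented as a pilot that should inform later trials, and its title centres on imaging. Nowhere does it say that success on any single outcome will be claimed. This is fair and lowers the stakes. Even so, the protocol makes a formal power calculation, sets a significance threshold and aims to explore a therapeutic effect, so the status of each outcome still has to be clear.
- **The SAP may handle multiplicity.** It may, and the absence of an adjustment method from this article is not the point. The point is that two sections disagree on what is primary and that no primary visit appears in the text. Both belong in the protocol.
- **Sizing on one of several primary outcomes is common.** It is, and the sample size section could be read that way. In that case the other three are primary without a sample size to support them, and the singular wording elsewhere remains unexplained.
- **The 24-test count.** A reader might infer that all four outcomes are tested at all six visits. The text says only that assessments take place then; it does not say that MRI and MRS are repeated each time, and the abstract points to fewer occasions. The 71% figure also needs repeated measurements on the same patients to be independent, which is implausible.
- **The 0.05 rule for imaging.** A reader might infer that fMRI and MRS are also judged at an unadjusted 0.05. That rule sits under clinical data; the imaging section states no threshold, and correction over regions is detail that an article commonly leaves out.

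**Conclusion.** The point holds as an internal conflict over the primary outcome together with a missing primary visit. If each of the four outcomes is tested once at 0.05 at one visit, familywise error is about 16% to 19%, which is three to nearly four times the nominal 5%. This rests on assumed between-outcome correlations of 0.5 to 0 and on 0.05 applying to imaging as well.

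The higher figures, 31% to 60% with assumed correlations and 71% as the independent limit, depend on a schedule that the text does not confirm and should be quoted only with that condition. In the other direction, the counts take one test per outcome and one group comparison; testing several regions, metabolites or group pairs without correction would raise them.

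Two stronger readings are not supported. A reader might conclude that a false positive primary result is more likely than not. That needs the fullest schedule with independent or only moderately correlated tests. A reader might also conclude that no primary outcome is named at all, but the sample size section does name MoCA. The fault is that this disagrees with the outcomes section.

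**What to change.** In the abstract, the Primary outcomes section and the Discussion, name one primary outcome: MoCA total score at week 8 (end of treatment), electroacupuncture versus sham. The choice of MoCA agrees with the sample size section.

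State one hypothesis and one alpha for that comparison. The sample size section describes a noninferiority comparison at 0.025 with a margin of −0.1 and does not say which two groups it compares; the analysis section uses two-sided tests at 0.05. Even if 0.025 is meant as one-sided, and so the same tail area, the hypotheses differ and must be reconciled.

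Treat CDR, fMRI, MRS and all other visits as secondary or mechanistic, reported with confidence intervals and without confirmatory claims.

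The cost is wording in the protocol, the registry entry and any SAP, with no added patients for the choice of primary outcome itself. The sponsor gives up the option of claiming a positive primary result on imaging or CDR alone, a real concession in a trial titled for its imaging effect. A ranked order that includes one named imaging measure would also remove the conflict. Keeping all four as equal primaries with a Bonferroni split would need about 44 per group in the illustration above.

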##### Montreal Cognitive Assessment Scale (MoCA)

This scale is an assessment tool for rapid screening of cognitive abnormalities. It is a validated scale for MCI in diabetes in China [19]. It includes 8 dimensions (attention and concentration, executive function, memory, language, visual structure skills, abstract thinking, calculation and orientation), with a total score of 30 and ≥ 26 points being normal. It is suitable for clinical applications because of its high sensitivity, coverage of important cognitive domains, and short testing time. However, it is also affected by education level, differences in cultural background, the examiner’s skills and experience in using MoCA, the environment of the examination, and emotional and mental state of the test taker will all affect the score. To correct the bias caused by education level, the total score is increased by 1 point for subjects with less than 12 years of education. This can better correct the bias caused by low education levels.

##### Clinical Dementia Rating (CDR)

This scale is a global dementia grading scale that assesses cognitive changes and determines the presence of dementia [20]. The scope of the assessment includes three cognitive domains (memory, orientation, judgment and problem solving skills) and three related activities of daily living skills (social interaction, family life, hobbies and self-care). The severity of dementia is quantified from very mild (CDR 0.5) to mild (CDR 1), moderate (CDR 2), and severe (CDR 3).

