## Background

Diabetes mellitus (DM) is a chronic disease that causes huge economic and social burdens. In recent years, a large number of studies have proven that DM has become an independent risk factor for cognitive impairment. The incidence of cognitive impairment is 1.5 times higher in type 2 diabetes mellitus (T2DM) patients than in non-DM patients [1], with 60 to 70% of T2DM patients having varying degrees of cognitive impairment [2]. Diabetic cognitive impairment (DCI) is a serious chronic complication caused by diabetes and is mainly manifested as deficiency of attention, visual structure, learning function, verbal memory, and calculation ability [3]. It is a state of cognitive impairment between brain aging and dementia that belongs to the early stage of Alzheimer's disease (AD) [4]. Serious cognitive deficits, especially in executive function, impact the self-care and medical compliance of these patients. DCI brings a serious burden to patients’ families and society, and thus effective prevention, early diagnosis, management, and treatment of DCI have become the focus of clinical research.

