### Inclusion criteria

Eligible participants for DCI subjects should meet the following inclusion criteria: (1) the 2020 American Diabetes Association Standards of Medical Practice for diabetes with a duration of ≥ 2 years; (2) signs or symptoms of memory loss; (3) Montreal Cognitive Assessment Scale (MoCA) score < 26 points, Clinical Dementia Rating (CDR) ≥ 0.5 points; (4) activities of daily living (ADLs) not significantly affected, and instrumental ability of daily living (IADL) score ≥ 16 points; (5) aged 50–70 years, with more than 6 years of education, able to complete a cognitive assessment; (6) sufficient visual and auditory discrimination to undergo neuropsychological testing; (7) no evidence of infection, infarction, or other focal injury, or associated clinical symptoms, as detected by transcranial CT or MRI in the 12 months prior to screening; allows for white matter lesions or cavitary infarcts in noncritical brain regions without affecting the subject’s cognitive function; and (8) signed informed consent, volunteered to participate in the study, and were able to cooperate with the physician in completing the clinical study. Eligible participants who meet the following inclusion criteria as healthy subjects: (1) conditions such as age and education that are comparable to other groups of subjects; (2) absence of significant neurological foci and absence of associated disorders that could cause cognitive impairment, as determined by cranial MRI; (3) no religious beliefs, no bad habits, such as tobacco, alcohol, coffee, and tea; (4) no job or life stress during the observation period; (5) in good health, free of cardiovascular and other organic diseases; (6) total MoCA score ≥ 26 points; and (7) signed informed consent, volunteered to participate in the study, and were able to cooperate with the physician in completing the clinical study.

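### CDR, a primary outcome, is described only as a coarse global grade in patients who probably mostly enter at 0.5, so it would respond poorly to anything short of a large effect

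*Protocol article*

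**What the plan says.** All places are in the Protocol article.

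- *Primary outcomes* lists imaging and spectroscopy together with "cognitive function assessed using the MoCA and CDR".
- *Clinical Dementia Rating (CDR)* introduces the instrument thus: "This scale is a global dementia grading scale that assesses cognitive changes and determines the presence of dementia". It names "three cognitive domains (memory, orientation, judgment and problem solving skills" and a further set of daily-living domains. The only quantity it then gives is the global grade: "The severity of dementia is quantified from very mild (CDR 0.5) to mild (CDR 1), moderate (CDR 2), and severe (CDR 3". No score is built from the domains, and no grade below 0.5 is named.
- *Inclusion criteria* requires "Clinical Dementia Rating (CDR) ≥ 0.5 points", with no upper limit, and "activities of daily living (ADLs) not significantly affected".
- *Background* says of diabetic cognitive impairment: "It is a state of cognitive impairment between brain aging and dementia". *Exclusion criteria* removes vascular dementia and neurological disorders that can cause dementia.
- *Setting of the study* plans "an 8-week treatment period, and a 6-month follow-up period", with assessments at baseline, at 4 and 8 weeks, and at 1, 2, 3 and 6 months after treatment.
- *Clinical data analysis* summarises clinical data as mean and standard deviation, uses paired t tests within groups, and compares changes between groups by analysis of variance or the rank-sum test. It also lists CDR among the variables turned into z scores for correlation with imaging.
- *Sample size estimation* rests on MoCA alone.

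**The concern.** An outcome used to judge treatment needs room to move in the patients who are enrolled. Here the selection rules narrow the spread of the very grade that is then used as an outcome. A patient who meets a pre-dementia description, has daily function largely intact and must score at least 0.5 most likely scores exactly 0.5, the lowest grade the article lists. The grade can record improvement in such a patient only if the whole grade is left behind. Partial gains in memory or orientation leave no trace, even though the scale is said to assess those domains.

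At stake is the reading of a primary outcome. A flat CDR next to a favourable MoCA would look like conflicting evidence when it may only reflect the coarseness of the grade. Tests on mean change would also be run on an ordinal variable taking very few values. For the third aim, which relates clinical change to brain change, CDR would contribute little information.

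**Working it through.** **The plan's own figure.** *Sample size estimation* gives about 24 per group on MoCA and 20% dropout: 24 / (1 − 0.20) = 30 per group, as stated. The 24 cannot be re-derived because no standard deviation or rate is given. That is a separate matter. No figure is given for CDR, so 24 and 30 per arm are used below as the evaluable and the randomised numbers.

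**Step 1: reduce the grade to what can be observed.** Assumptions: every patient enters at 0.5; a better grade of 0 exists (the article does not name one); worsening is set aside. Improvement is then a yes/no outcome with probability p1 under electroacupuncture and p0 under sham. The difference in mean grade is 0.5 × (p1 − p0). For 30% versus 10% this is 0.5 × 0.20 = 0.10 points; for a 10-point difference it is 0.5 × 0.10 = 0.05 points. The rates are illustrative, since the protocol states none.

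**Step 2: exact power.** For each pair of improvement counts (a, b) out of n per arm, take the product of the two binomial probabilities, and sum it over the pairs for which the two-sided Fisher test gives p < 0.05.

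| Improving, electroacupuncture v sham | n = 24 per arm | n = 30 per arm |
|---|---|---|
| 15% v 5% | 0.106 | 0.093 |
| 20% v 10% | 0.097 | 0.096 |
| 30% v 10% | 0.314 | 0.372 |
| 40% v 10% | 0.602 | 0.705 |
| 50% v 10% | 0.834 | 0.914 |

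**Step 3: is this only Fisher's conservatism?** Fisher's test is not the planned analysis. Repeating the enumeration with a two-group t test on the change (0 or −0.5) gives power of 0.17 to 0.26 for the two 10-point rows and 0.43 (n = 24) to 0.50 (n = 30) for 30% versus 10%. The rank-sum test without continuity correction gives the same values. Power is higher but still poor.

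**Step 4: what can be detected.** By the normal approximation at two-sided 0.05 and 80% power, the electroacupuncture rate would have to be:

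| Sham rate | n = 24 per arm | n = 30 per arm |
|---|---|---|
| 0% | 27% | 22% |
| 5% | 37% | 33% |
| 10% | 45% | 41% |
| 20% | 59% | 54% |

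The required differences run from 22 points (22 − 0) to 39 points (59 − 20).

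**Step 5: the alternative.** The article names three cognitive and three daily-living domains but gives no scoring for them. If each of the six were rated 0 to 3 (an assumption), their sum would run from 0 to 6 × 3 = 18, so a gain in a single domain would register.

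**The case against.** The strongest reply is that the CDR section describes an instrument and does not define an endpoint. Neither *Primary outcomes* nor *Clinical data analysis* says in terms that the global grade is the analysed variable, and a condensed article may leave that to the full protocol. This has some weight. Still, the article does give one quantification of CDR, and it is the global grade. The point is that this quantity suits the selected population badly, not that a detail is absent.

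Several stronger readings are tempting, and the documents do not support them:

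- *That CDR cannot show improvement.* A reader might infer this, but 50% versus 10% has 83% exact power with 24 per arm. The grade is insensitive, not incapable.
- *That nearly all patients enter at 0.5.* This is a reasonable inference, not a stated fact. The criterion has no ceiling and no baseline distribution is given. A patient entering at 1 could improve to 0.5, though still only by a whole grade.
- *That only one downward step within 8 weeks is possible.* Assessment runs to 6 months after treatment, and worsening to 1 can be recorded. Worsening matters because the second aim includes prevention. Longer follow-up adds time for change but no finer resolution.
- *That the trial or its third aim fails.* MoCA and imaging are also primary, MoCA is the sizing outcome, and MoCA too is correlated with imaging. The loss to the third aim is partial.

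It is also fair to say that grade 0 and the 0 to 3 domain scoring come from outside the article. They are therefore marked above as assumptions.

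**Conclusion.** The point holds as one of poor responsiveness. CDR is a primary outcome, the only quantity described for it is a four-level global grade, and the entry rules probably place most patients at the lowest of those levels. If all entered at 0.5, exact power would be about 10% for the 10-point differences examined and 31% to 37% for 30% versus 10%. Differences of roughly 22 to 39 points would be needed for 80% power, depending on the sham rate and the evaluable number. These figures rest on assumed improvement rates and on the assumed common entry grade; they illustrate the scale of the problem and do not predict the result. A null CDR finding should not be read as no cognitive benefit. The remedy is worth making, but the trial does not stand or fall on it.

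**What to change.** Keep the global CDR grade for eligibility, and report it afterwards descriptively as the proportion improving, unchanged or worsening by a grade. As the CDR outcome, use the sum of the domain ratings from the same interview, as change from baseline, electroacupuncture versus sham, at the visits already scheduled. State how each domain is scored and what range the sum has. If the ratings cannot be obtained, move CDR out of the primary set and say that its global grade is expected to be insensitive in these patients.

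The cost is a change of outcome wording and space on the case report form for the domain ratings, with no added visit, instrument or patient. *Trial status* shows the study already under way, so the change should be a dated amendment made before any unblinded look at the data. It should also say whether domain ratings were kept for patients already assessed, which the article does not tell us.
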